
### 2.5. Outcomes

The primary clinical outcome will be a composite of at least one event, including emergency department visits or hospitalization for related pathological causes. This outcome will be evaluated pre- and post-intervention to assess the effectiveness of the proactive care on hard endpoints. On the other hand, secondary outcomes will be assessed after the intervention in terms of the following:Medication adherence through the calculation of the periods elapsed between prescriptions;Self-care ability assessed using the Patient Activation Measure (PAM) [41];Quality of received care by Patient-Reported Experience Measurement (PREMsT questionnaire).

The following process evaluations will also be collected during the reference period:Number of patients with periodic use of the nursing service (at least three visits);Number of nursing visits for each user;Number of nurse visits at home;Number of users that received structured family assessment interviews;Number of medical visits by the general practitioner for each user;Rate of users with new prescriptions of aids/devices;Number of services activated per person: physiotherapist, palliative care, social worker, etc.;Rate of users reported to the general practitioner for suspected exacerbation of chronic pathology.

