Throughout all interviews, four communication approaches will be implemented:(a)Teach-back [34,35]: This is a communication strategy designed to assess an individual’s understanding of newly acquired information. After presenting the information incrementally, the individual is asked to summarize what has been understood using their own words, thereby identifying any knowledge gaps. This approach actively engages the participant and holds the professional accountable for effective communication, ensuring that information is conveyed in small, manageable portions and comprehension is verified at each step.(b)Motivational Interviewing [36,37]: This is an evidence-based counseling style that facilitates a collaborative dialogue within a supportive and empathetic environment. This approach aims to elicit the individual’s intrinsic reasons for change and strengthen their commitment and motivation to achieve specific goals. The primary components include reflective listening, open-ended questions to elicit change-oriented statements, synthesis and support affirmations, and targeted information.(c)Sharing Evidence Routine for a Person-centered Plan for Action (SHERPA model) [38,39]: This is a structured three-phase shared planning approach. In Phase 1 (Share), the individual’s problems are identified collaboratively, including illnesses related to physical and emotional elements (diagnosis, behaviors, symptoms, concerns, emotions), social issues such as isolation or poverty, and challenges in disease management, aiming to create a person-centered problem framework rather than a diagnosis-focused one. In Phase 2 (Link), the professional and the patient discuss how to connect these issues, mapping them visually in circles of varying sizes proportional to their significance. Pathophysiological connections help the individual understand their condition, while the patient’s connections provide insights into personal values, beliefs, and non-clinical expectations. In Phase 3 (Plan), the professional and the individual prioritize these issues and set specific goals, such as reducing medication, managing symptoms, modifying unhealthy behaviors, or achieving social objectives.(d)Interviews with family units, inspired by the Calgary Family Assessment and Intervention Models [40]: These shift the focus away from the individual patient, are designed to support families as a unit, and are particularly effective when families experience physical and emotional distress and face challenges in response to stressful events such as death, end-of-life care, or acute and chronic illnesses. By employing a systematic approach to family assessment—investigating structural, developmental, and functional categories, along with genograms and ecomaps—the nurse can identify family strengths and resources within the caregiver network and formulate appropriate interventions. Such interventions may include providing information and perspectives, using questions to promote change in the affective, behavioral, and cognitive domains of family functioning, encouraging family members to assume or relinquish caregiving roles, and activating community and social resources to support the family.

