### 2.6. Data Collection

All data needed for the analysis, meaning outcome measures, socio-demographic data, and assessment evaluations, will be computed pseudonymized in a different Excel file, secured by the research network. Information will be collected from nurses’ Excel charts and databases already in use by the pharmacy service and hospital facilities. The region shares an integrated electronic database that provides access to data from all surrounding facilities. Data collection will be carried out for the primary outcome over 12 months before and over 12 months after enrollment, and for secondary outcomes through 6 and 12 months following enrollment (Table 1). Specifically, questionnaires on self-care and the quality of received care will be administered at three time points: enrolment, 6 months, and 12 months. To establish the correlation between hospitalization and patients’ underlying chronic diseases, hospital discharge records, IDC codes, and discharge summaries will be assessed. When ICD codes do not specifically refer to “exacerbation” or “acute on chronic” or “decompensated” condition, the discharge letters will be analyzed, searching for the same information. When these criteria are not met, hospitalization will be considered generic, and two GPs will be involved to assess the correlation; any disagreement will be resolved through discussion.

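### As the text stands, medication adherence has no pre-enrolment value, so this single-group pre–post study cannot estimate a change in it

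*Protocol article*

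**What the plan says.** All references are to the protocol article.

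- **Measure (2.5).** The first secondary outcome is "Medication adherence through the calculation of the periods elapsed between prescriptions". No scoring rule is given.
- **Timing in 2.5.** The primary composite is evaluated before and after the intervention. By contrast, "secondary outcomes will be assessed after the intervention".
- **Timing in 2.6.** Data are collected "for the primary outcome over 12 months before and over 12 months after enrollment" and "for secondary outcomes through 6 and 12 months following enrollment". The section then states that the self-care and quality-of-care questionnaires are also given at enrolment. Adherence is not mentioned there.
- **Source (2.6).** Information comes from the nurses' charts and "databases already in use by the pharmacy service and hospital facilities".
- **Intervention (2.4).** In the planning phase of the SHERPA approach, nurse and patient "set specific goals, such as reducing medication, managing symptoms", among other examples.
- **Analysis (2.8).** Wilcoxon signed-rank and McNemar tests are planned for pre–post comparisons, and GEE models for change over time. The outcomes for each are not named.

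**The concern.** Section 3 acknowledges that there is no counterfactual group. Each patient's own earlier value is therefore the only reference against which an outcome can be judged. An outcome first measured after the intervention has begun has no such reference: its level can be described, but a change cannot be attributed even provisionally to the programme.

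Adherence is one of only three secondary outcomes, and Section 3 intends to discuss observed effect sizes. If the text is followed literally, there will be no effect size for adherence, even though the data source is one that could plausibly supply the earlier period.

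A second, lesser matter is the measure itself. The interval between prescriptions responds to things other than adherence. One is a reduction agreed with the patient, which the intervention may itself bring about. Another is time in hospital, which is part of the primary outcome.

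**Working it through.** **Step 1. Timing, outcome by outcome, from the running text of 2.5 and 2.6**

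| Outcome | Before or at enrolment | After enrolment |
|---|---|---|
| Composite of ED visit or hospitalization | 12 months before | 12 months after |
| PAM | at enrolment | 6 and 12 months |
| PREMsT | at enrolment | 6 and 12 months |
| Medication adherence | none stated | 6 and 12 months |

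Table 1 might fill the empty cell, but its marks are lost in the copy reviewed for almost every row, so it neither confirms nor refutes a pre window.

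**Step 2. What can be estimated from that schedule**

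The within-patient change is (post value − pre value). Wilcoxon and McNemar both need the pair. With no pre value, the only available contrast for adherence is 12 months against 6 months. Section 2.3 starts the contacts at enrolment and spreads at least three over six months, so both readings follow the start of the intervention. That contrast shows a later trend under the programme, not a before–after effect.

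**Step 3. How a gap-based measure behaves**

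The plan has no figure to reproduce. The following is an illustration. All inputs are assumed: 30-day packs, a 182-day window, and a patient who takes every dose as currently prescribed. With no change of regimen, the mean gap is 30 days.

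*Use halved by agreement, same pack lasting 60 days afterwards:*

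- from day 60: gaps 30, 30, 60, 60; mean 180/4 = 45.0 days
- from day 90: gaps 30, 30, 30, 60; mean 150/4 = 37.5 days
- from day 120: gaps 30, 30, 30, 30, 60; mean 180/5 = 36.0 days

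*Drug stopped by agreement:*

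| Stop day | Mean gap between consecutive prescriptions | Mean gap if the open interval to day 182 counts | Days covered, not censored | Days covered, censored at stop |
|---|---|---|---|---|
| 60 | 30 | 182/2 = 91.0 | 60/182 = 0.33 | 1.00 |
| 90 | 30 | 182/3 = 60.7 | 90/182 = 0.49 | 1.00 |
| 120 | 30 | 182/4 = 45.5 | 120/182 = 0.66 | 1.00 |

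Reduced use lengthens the gap directly. A complete stop does not, unless the open interval is counted or coverage is left uncensored.

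**Step 4. Two further illustrations on a coverage scale, inputs again assumed**

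- Six drugs at 80% coverage, one stopped halfway through the window: (5 × 80 + 40)/6 = 73.3%, an apparent loss of about 7 points.
- A 14-day stay supplied by the ward in a 180-day window: 14/180 = 7.8%, so up to about 8 points.

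These show direction and order of magnitude only. The article specifies intervals rather than coverage, and says nothing about how often such events occur.

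**The case against.** The strongest reply is that the absence of a baseline is inferred from silence. The general sentences in 2.5 and 2.6 cover all secondary outcomes, yet PAM and PREMsT turn out to have an enrolment value, so those sentences do not by themselves exclude one for adherence. The sentence on three time points concerns questionnaires that are administered, whereas adherence comes from records. Section 2.6 also points to Table 1 for timing. This stands as a limit on certainty: a pre window in the table cannot be ruled out. It does not remove the point, because the text would then disagree with the table and need correcting.

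A reader might also infer that agreed medication reductions are counted as non-adherence. The article does not support that. It names a construct and gives no threshold, coverage ratio or rule for stopped drugs or inpatient days; such detail may sit in the full protocol or analysis plan. Step 3 shows that a complete stop need not lengthen the gaps at all. Nor is reducing medication the aim of the intervention: it is one example among several individually agreed goals. What remains is a risk to be handled explicitly, not an error already made.

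Finally, this is one secondary outcome in a study that disclaims inferential ambition (Section 3). That limits the consequence. A descriptive effect size, however, needs a baseline just as much as a test does.

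**Conclusion.** The point holds in this form: the running text places adherence only after enrolment, while every other primary or secondary outcome has a pre-enrolment or enrolment value. Followed as written, the design yields no before–after estimate for adherence, and comparing 6 with 12 months does not replace it. What is lost is the whole pre–post contrast for one of three secondary outcomes; the primary outcome is unaffected.

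This rests on reading 2.5 and 2.6 as complete on timing, with Table 1 unable to settle the matter.

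The vulnerability of gap-based measurement is a secondary, conditional point. It is real for reduced use (36–45 days against 30 in the illustration). For complete stops it depends on a scoring rule that the article does not give. The 7- and 8-point figures are illustrations, not estimates of bias in this trial. The change is cheap and should be made.

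**What to change.** 1. **State the windows.** Say in 2.5 and 2.6 that adherence is also measured over the 12 months before enrolment, as the primary outcome is, and bring the text and Table 1 into agreement.
2. **Extract the earlier period.** Obtain prescription records for those 12 months from the pharmacy database. This assumes that it holds that period; the article says only that the databases are already in use.
3. **Use one rule before and after.** Define adherence as the proportion of days covered for each chronic drug. Identify discontinuations and inpatient days identically in both periods, from prescription and hospital records alone. This assumes that the records allow days' supply to be derived.
4. **Analyse the within-patient change** between pre and post values.
5. **Keep the nurses' medication plan out of the main calculation.** It starts at enrolment. Using it to remove agreed stops only afterwards would raise post-period coverage relative to the pre-period and favour the intervention. Use it in a post-period sensitivity analysis.

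The cost is a wider date range in an extraction that is already needed, plus standard code. The downside is that reasons for discontinuation before enrolment are less well documented. A rule based on records alone cannot separate an agreed stop from an abandoned drug; it treats both periods alike, and this limit should be reported.

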### 2.4. Intervention

The intervention will be the only manipulated variable, as the nurses involved are the same that would have been leading care for patients and their informal caregivers within the Community Home. Nurses will conduct a therapeutic education program following standard components developed based on multiple frameworks, theories, and evidence, focusing on behavioral changes [27], enhancing engagement and empowerment [28,29], self-care and symptom management [25,26,30], and planning health promotion strategies [31].

Specifically, during the first interview, the nurse will collect the following data.

(a)Socio-demographic status and family network: age, sex, cohabitation status and designated caregiver(s).(b)Patient and caregiver’s priority needs, capturing concerns, difficulties, and expectations with open-ended questions.(c)Clinical condition: vital signs, BMI, diseases and related medications, civil disability status, medical exams, and blood tests.(d)Socio-educational needs, meaning the following:
Lifestyles, combining physical activity, sleeping quality, alcohol consumption, and smoking habits;Self-care skills, using the Patient Activation Measure (PAM) questionnaire [32];Clinical–social frailty, assessing the risk with the Sunfrail questionnaire [33].

Other specific questionnaires will be used whenever concerns or issues are faced. All questionnaires that will be administered are validated in Italian; for each patient, scores will be collected in a specifically designed Excel file. This spreadsheet will serve as electronic documentation, including questionnaires, automated scoring, a summary of active clinical and educational issues, a medication plan, and goals shared with the patient. These elements will be prefilled based on nurses’ data input and finalized manually. The tool will serve as a guide for nurses to deliver the intervention and will become part of the healthcare electronic system. All information will be incorporated into an educational plan, which will be provided to the patient in written form.

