## Figures and Tables

**Figure 1 healthcare-14-01830-f001:**
[figure not shown]
The figure illustrates the educational pathway of the intervention, detailed below. The first box represents the initial assessment, followed by the definition of problems and goal setting. Through the process, nurses will collect data and also carry on the educational intervention with multiple techniques. The resulting tailored plan will be monitored and improved through follow-up sessions.

**Table 1 healthcare-14-01830-t001:** Outcomes and data collection points.

	T-1 (12 Months Before Enrolment)	T0 (Enrolment)	T1 (6 Months)	T2 (12 Months)
Composite outcome (access ED or hospitalization)	PRE 	POST 		
Medication adherence (Periods elapsed between prescriptions)				
Self-care ability assessed (PAM questionnaire)				
Quality of received care (PREMsT questionnaire)				
N. patients with a periodic use of nursing service (≥3 visits)				
N. of nursing visits for each user				
N. of medical visits by the general practitioner for each user				
N. of nurse visits at home				
N. of users with family assessment interviews				
Rate of users with new prescriptions of aids/devices				
N. of services per person (physiotherapist, social worker, etc.)				
N. of users reported to the general practitioner for suspected exacerbation				

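### As worded, medication adherence is the time between prescriptions, which takes no account of whether the medicine was collected or how many days it covered

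*Protocol article*

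**What the plan says.** Section 2.5 (Outcomes) lists as the first of three secondary outcomes "Medication adherence through the calculation of the periods elapsed between prescriptions". Table 1 repeats the definition: "Medication adherence (Periods elapsed between prescriptions". Neither place mentions dispensing, collection, refill or days' supply.

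Section 2.6 (Data Collection) gives the sources for all outcomes together: "Information will be collected from nurses’ Excel charts and databases already in use by the pharmacy service and hospital facilities". It does not say which source supplies adherence, or whether the pharmacy records hold prescriptions written or medicines handed out. No general-practice prescribing database is named.

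On timing, section 2.5 says "secondary outcomes will be assessed after the intervention in terms of the following", and section 2.6 says "for secondary outcomes through 6 and 12 months following enrollment". The readable text states no pre-enrolment period for adherence. The time-point marks in Table 1 are not legible in the copy at hand.

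Section 2.4 (Intervention) says that the nurses' spreadsheet contains "a medication plan, and goals shared with the patient". The description of the shared-planning approach in the same section allows reduction of medication as one of the goals that nurse and patient may set.

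**The concern.** The programme is educational, and its adherence outcome should show what patients do with their medicines. In ordinary use a prescription is the prescriber's act. If the interval between prescriptions is taken as adherence, two things go wrong.

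- **Collection is not seen.** A prescription renewed on time but never collected counts in full.
- **Quantity is not seen.** The same interval can mean complete or incomplete cover, depending on how many days' supply was given.

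The published figure would then be partly a description of prescribing. That matters because adherence is the only one of the three secondary outcomes not based on a questionnaire, and because the study has no comparison group against which a change in prescribing habits could be recognised.

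**Working it through.** The plan states no figure for this outcome, so there is nothing to reproduce. The check sets the definition against the listed sources and then illustrates what the definition does.

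**Definition against sources.** Sections 2.5 and Table 1 name one event, the prescription. Section 2.6 names three kinds of source: nurses' charts, pharmacy-service databases and hospital databases. Two readings remain open:

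- *Literal reading:* the date of each prescription is counted, collected or not.
- *Dispensing reading:* prescriptions means prescriptions filled, as a pharmacy database might record them.

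Nothing in the article decides between them.

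**Illustrations.** All inputs are assumptions: a 360-day observation period and 30 days' supply per prescription. Coverage = days' supply counted / days observed.

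1. *Uncollected prescriptions.* Twelve prescriptions are written on time.
   - Literal: 12 × 30 / 360 = 100%.
   - Dispensing: 100% × share collected. For shares of 100%, 90%, 80% and 70%, coverage is 100%, 90%, 80% and 70%.
   - Overstatement: 0, 10, 20 and 30 percentage points.

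2. *More regular prescribing, same collection.* Prescriptions written rise from 10 to 12, while 10 are collected in both periods.
   - Literal: 10 × 30 / 360 = 83%, then 12 × 30 / 360 = 100%.
   - Dispensing: 83% in both periods.
   - The literal score rises by about 17 points with no change in what the patient obtained.

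3. *Medicine stopped by agreement.* Ten prescriptions are written and collected on time, and the medicine is then stopped by agreement at day 300.
   - Over the full period: 10 × 30 / 360 = 83%.
   - Over the days the medicine was intended: 300 / 300 = 100%.
   - The score falls by about 17 points with no non-adherence.

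4. *Quantity.* Ten prescriptions evenly spaced over 360 days give an interval of 360 / 10 = 36 days.
   - With 30 days' supply each, cover is 30 / 36 = 83%.
   - With 36 days' supply each, cover is 36 / 36 = 100%.
   - The interval is 36 days in both cases, so interval length alone cannot tell them apart.

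On the dispensing reading, the overstatement in illustration 1 and the spurious rise in illustration 2 are both zero. Illustrations 3 and 4 apply on either reading for as long as the measure is interval length alone.

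**The case against.** The strongest reply is that the authors probably mean dispensed prescriptions. The article never says that the dates are those of issue, it names no prescribing database, and the pharmacy service is the most plausible listed source for medication dates. This carries weight: if it is right, the problem of uncollected prescriptions disappears and the correction is mainly one of wording. It does not close the point, because section 2.6 ties no source to this outcome and does not describe what the pharmacy records contain.

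A second reply is that the algorithm belongs in the full protocol or analysis plan, which is not shown. Thresholds, drug classes and handling of hospital stays may indeed be set there. But the article commits to a specific measure. An analysis plan that keeps it inherits the weakness, and one that uses dispensing departs from the published definition.

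A reader might go further and infer that the programme can raise the score simply by prompting renewals, so that the error favours the programme. The documents do not support this:

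- No prompting of renewals is described.
- The reporting of patients to the general practitioner is limited to suspected exacerbation.
- Counting general-practitioner visits is a process measure, not part of the intervention.
- Agreed reduction of medication would push the score the other way.
- An apparent before-after gain would need a pre-enrolment value, which the readable text does not state for adherence. A constant unfilled share would shift the level without creating a change.

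Finally, the limitations section disclaims inferential conclusions. That lowers the stakes, but a descriptive adherence figure still has to describe adherence.

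**Conclusion.** The point stands as a weakness in a stated outcome definition. As worded, the measure counts prescriptions, not medicines obtained, and takes no account of quantity. It can therefore misstate the level of adherence and mix prescribing with patient behaviour.

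The size is unknown. The range of 0 to 30 percentage points rests on assumed fill shares of 100% down to 70% and on the literal reading; if dispensing records are used, that part is zero. The direction is not established. It would be wrong to state as fact that dates of issue will be used, since the article leaves this open.

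Severity is low to moderate: one of three secondary outcomes is affected, the primary outcome is untouched, and the correction is simple.

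**What to change.** In section 2.5 and Table 1, define medication adherence as days covered, calculated from dispensing dates and quantities in the pharmacy-service database already named in section 2.6, and name that database as the source for this outcome. State that medicines stopped or reduced by agreement are not counted as non-adherence from the date of the change.

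First confirm which fields the database holds. If it holds only prescription dates, keep the interval but move it to the process evaluations as a measure of prescribing, and do not call it patient adherence.

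The cost is a change of wording and of the variables extracted, with no new source if the database records dispensing. There are two drawbacks: medicines obtained outside the recorded system will not be seen, and reported adherence may be somewhat lower than under the present wording. The rule on agreed changes also requires their dates to be recorded; the medication plan in the nurses' spreadsheet is a natural place for them.
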